## Abstract

**Background:**

Many factors influence housing choices among older adults, but far from all have been identified. There is little systematic analysis that has included economic factors and virtually no knowledge about the interplay among perceived costs of moving, health status, and the mobility rate of older homeowners. It is currently unclear whether economic factors influence older adults’ willingness to move, and the effects of economic policies on their actual behavior in the housing market are largely unknown.

**Objective:**

The overarching objective of the AGE-HERE project is to develop knowledge of the relationship between health and economic factors that incentivize or disincentivize relocation during the process of aging.

**Methods:**

This project uses a mixed methods convergent design across 4 studies. The initial quantitative register study and subsequent qualitative focus group study will nurture the evidence base and the development of a national survey. The final study will synthesize and integrate the results of the entire project.

**Results:**

Ethical approval for the register study (DNR 2022-04626-01) and focus group study (DNR 2023-01887-01) has been obtained. As of July 2023, data analyses (register study) and data collection (focus group study) are currently being conducted. The first paper based on the register data is expected to be submitted after the summer of 2023. Three meetings have been held with the nonacademic reference group. The qualitative data will be analyzed in the autumn. Based on the results of these studies, a survey questionnaire will be developed and distributed nationally during the spring of 2024, followed by data analyses in the autumn. Finally, the results from all studies will be synthesized in 2025.

**Conclusions:**

Results from AGE-HERE will add to the knowledge base for research on aging, health, and housing and can play a critical role in guiding future policy decisions aiming to balance the housing market. Such developments may lower related social costs and support older adults to maintain active, independent, and healthy lives.

**International Registered Report Identifier (IRRID):**

DERR1-10.2196/47568

## Introduction

### Background

The aging population increases the demand for housing adapted to diverse needs that facilitates active and healthy aging [1]. However, this demand is far from met because older adults face a challenging housing market with few choices available [2]. In Sweden, the supply of newly built homes has not kept pace with the increasing demand, and municipalities experience housing shortages [2], which has a major impact on individuals as well as on economic growth. Reforms have been implemented, and further reforms have been discussed. However, the housing policy debate has largely been based on increasing housing construction rather than finding ways to make better use of the existing housing stock.

According to the public debate, older homeowners are concerned about the costs associated with moving (eg, higher rental costs, a monthly association fee, and bank policies) [3]. At the same time, the housing market is experiencing insufficient residential mobility and inefficient relocation chains [2]. However, studies on housing and health in later life seldom incorporate economic factors [4], and how such factors influence older adults’ willingness to move is currently unknown. A better understanding of these relationships can play a critical role in guiding future policy decisions aiming to balance the Swedish housing market, which in turn may lower associated economic and social costs as well as support older adults to maintain active, independent, and healthy lives.

Older adults spend more time at home compared to other age groups, and therefore, it is important that the home environment is adapted to suit their needs and preferences. Thus, as people age, housing is associated with health outcomes [5-8]. For example, accessibility problems in the home may lead to injuries and social isolation, which in turn have negative health effects [9]. Yet, research on factors that contribute to residential mobility for those who wish or need to move is sparse [8]. Given that older adults represent a group with varying housing preferences and needs [10,11], more knowledge is needed to support the development of future housing policies that accommodate this heterogeneity.

Recent international research has primarily focused on relocation to residential care facilities [12-14], with disabilities and frailty as predictors of relocation [15]. Situational circumstances such as strong community ties and individual or family health, in combination with social and economic conditions, make housing decisions complex in older age [16]. Thus, negotiating relocation is described as a long process until turning points emerge [17,18]. While these studies primarily focus on the very old, a recent study using register data from the United States showed that factors such as a change in income, years living in the community, and degree of social support are important characteristics for predicting relocations among persons in early retirement age [10]. Adding to this, qualitative research from Sweden suggests that older adults start to have more active reflections regarding their future housing choices and relocations around retirement age [19]. While some studies indicate that retirement triggers actual moves [10,20], we do not know whether economic issues encourage this younger group of older adults to stay in privately owned houses longer, even though those no longer suit their needs and preferences. This knowledge is crucial, especially during times of economic uncertainty and rapid social change, as it can assist policymakers in making informed decisions that support older adults in making suitable housing choices and enhancing their overall well-being.

Turning to the economic situation on a national level, macroeconomic trends such as booms or recessions, usually measured by gross domestic product growth, are likely to influence individuals’ behavior in the housing market. This might be especially true for homeowners, as they often have most of their savings invested in the house and can therefore be affected by changes related to the housing market, such as house prices and interest rates [21]. Yet, the majority of studies on this topic focus on the entire population [22] rather than specific age strata, such as older adults. One exception is a study conducted in the United States evaluating lock-in effects due to the financial crash in 2008 and a subsequent major decrease in housing prices. The authors found that the probability of downsizing for adults aged 55 years and older was higher among people with a higher loan-to-value ratio (measured by mortgage loans or value of the house) compared with owners with a lower ratio [23]. Hence, it is likely that economic fluctuations influence households differently, but how such associations develop over time and emerge in a Swedish context remains unknown.

### Housing Policy Context

The AGE-HERE project focuses on homeowners aged 55 years and older. In Sweden and most other Organisation for Economic Co-operation and Development (OECD) countries, the most common form of tenure among this age group is single-family home ownership [24,25]. This age group often has most of their savings invested in their house, and other available assets are limited [21], which makes them more vulnerable to changes related to the housing market, such as interest rates or housing prices. As to other economic factors, several have been suggested to encourage this population segment to stay in their current home rather than move. The 2008 Swedish property tax reform lowered the yearly property tax on especially highly assessed property by introducing a low maximum amount, but the capital gains tax was raised from 20% to 22%. Taken together, these changes increased the incentives to stay in large houses rather than moving to smaller ones. In addition, rent control has reduced the supply of apartments, which increases the price of other types of housing, such as owner-occupied housing [3]. Hence, it is likely that the way housing is taxed influences people’s relocation behavior, which calls for more research in this area.

### Study Objective and Research Questions

AGE-HERE aims to develop new knowledge on relationships between economic factors and health that incentivize or disincentivize relocation among homeowners from an early stage of the aging process (55 years and older). The specific research questions are as follows:

How did macroeconomic events during the period 1970-2016 affect relocation patterns across time for older homeowners of different ages? Are there different patterns of relocation depending on civil status and sex?In what way did the tax reform of 2008 affect the probability of moving among older homeowners?What economic factors predict relocation to different types of housing (eg, condominiums, owner-occupied housing, and rental apartments), taking health factors into account?What economic and health factors do older homeowners perceive as important when considering relocation?What are older homeowners’ preferences and beliefs regarding the economic factors that disincentivize or incentivize relocation?To what extent do older homeowners report that economic factors are an important part of the relocation decision process?How are economic factors and health related to decisions to move among older homeowners?How are the questions above affected by regional differences and housing market structures?

### Framework

As a starting point, we will use a framework developed by Roy and coauthors [4] to conceptualize and examine the complexity of factors associated with housing decisions in older age. Covering 6 dimensions—socioeconomic and health, built and natural environment, social, time and space, psychological and psychosocial, and housing economics—this framework is a useful tool to build ties between different research fields [26]. With this framework as the starting point, we will combine several bodies of theories used in research investigating housing decisions in older age: environmental press, migration theory, residential normalcy, and control [4].

Deciding to relocate or not is influenced by individual health factors such as functional limitations and environmental factors [4], which is in line with the environmental press theory stating that the relationship between a person and their environment (social, environment, policy) affects their well-being and behavior [27,28]. Additionally, migration theory covers several domains described by Roy et al [4] and is important to elucidate the place- and people-based push and pull factors that influence older adults’ decisions to relocate, particularly after retirement [29]. For example, while investment and housing value may be important for the decision to remain in a current home, stressors such as poor health, safety concerns, mortgages, and tenure status might manifest as push factors leading to a decision to relocate. In parallel, we will draw upon theories relating to the concepts of space (ie, housing, the physical dwelling) and place (ie, a home, with personal meanings) [28]. Thus, the meaning assigned to a home impacts the decision to relocate, and moving into a new home initiates a process of recreating meaning in the new place through living there [28]. These are important aspects in the time and space dimensions as well as in the psychosocial dimension of Roy et al’s [4] framework. From an economic perspective, we will use the life cycle hypothesis, which predicts that households favor smooth rather than uneven consumption over their life cycle. In line with the economic factors (eg, mortgages, relocation costs, and taxes) described as important in the framework, the life cycle hypothesis implies that older adults who view their property as part of their retirement savings would sell their property in favor of renting or moving to a smaller, less costly home (ie, to increase the possibility to consume). In addition, tax theory, specifically the principles of tax neutrality and economic efficiency [30], is relevant. For taxes to be efficient, they should be designed so they do not influence behavior (eg, consumption and investments) [30], but when diverse types of housing are taxed differently (as in Sweden), taxes will steer behavior toward types of housing with beneficial taxation. That is, in contrast to the prediction of the life cycle hypothesis described above, the Swedish tax system may disincentivize relocation, so older adults remain in their homes even if that is not what they prefer.

## Methods

### Overview

AGE-HERE has 4 parts (Figure 1): a register study, a qualitative focus group study, a national survey study, and an integration study. The project is conducted in collaboration with a reference group consisting of nonacademic partner representatives (eg, housing market experts and senior citizen organization representatives) who will provide their input and reflections throughout the research process.

**Figure 1 figure1:**
[figure not shown]
AGE-HERE project design; mixed methods convergent design.

### Study Design

AGE-HERE has a mixed methods approach in a convergent design [31]. Results from the initial quantitative and qualitative studies will be used to develop a quantitative national survey. The final study will synthesize and integrate the results of the entire project (Figure 1).

### Register Study

To investigate how macroeconomic events and taxes on property and capital gains affect relocation patterns for older homeowners, we will use data from several registers such as the Longitudinal Individual Data Base, a longitudinal database with a representative sample of the population in Sweden (N=300,000) from 1968 to 2016, and the income and taxation register, which provides information related to taxation and income for the entire population of Sweden. To analyze different factors, we will link data from the Longitudinal Individual Data Base and the income and taxation register to register data on health and housing, for example, from the property register, the population register, and the patient register.

### Analysis

#### Tax Reform 2008

Differences-in-difference analysis [32] will be used to study the effects of the tax reform of 2008. Detailed information about taxes and income sources, as well as types of housing and socioeconomic variables, will be used to compare households that were affected to a large extent by the tax reform, that is, those living in highly assessed properties (high exposure group), with those that were less affected, that is, those living in properties worth less (low exposure group). The differences in the number of moves between the high and low exposure groups 2 years prior to the reform (2006) with the differences in the number of moves in the same groups 2 years after the reform (2010) will be compared. As this is not a randomized experiment, 3 methods to adjust for potential systematic differences between the groups will be used. First, we will control for variables such as income, education level, and place of residence that may affect the 2 groups differently. Second, we will use a propensity score matching technique [33] to determine a matched comparison group. Third, we will use a regression discontinuity design to evaluate the effect of the 2008 tax reform. Because the 55 years and above age group is heterogeneous, we will investigate whether different groups are more or less sensitive to economic factors. More specifically, we will compare different subgroups such as age cohorts, retired or working, have been or are receiving sickness payments, marital status, and sex.

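### The tax-reform difference-in-differences rests on one year before (2006) and one year after (2010), so parallel trends cannot be examined and any trend or 2008 downturn effect that differs by property value would be read as a reform effect

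*Protocol article*

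**What the plan says.** In the protocol article, the section Tax Reform 2008 names the method: "Differences-in-difference analysis [32] will be used to study the effects of the tax reform of 2008". Exposure is defined by property value, comparing "those living in highly assessed properties (high exposure group), with those that were less affected" by the reform. The contrast is then fixed in time: "The differences in the number of moves between the high and low exposure groups 2 years prior to the reform (2006" on one side, and the corresponding differences "in the same groups 2 years after the reform (2010) will be compared" on the other. No other year is named, and there is no mention of a pre-trend check or a placebo period.

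Because the comparison is not randomised, three adjustments follow: covariates ("we will control for variables such as income, education level, and place of residence"), propensity score matching, and a regression discontinuity design. No running variable or cut-off is given for the last.

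Three other places bear on this:

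- **Register Study** describes the main source as "a longitudinal database with a representative sample of the population in Sweden (N=300,000) from 1968 to 2016".
- **Background** places a financial crash in the reform year and cites a United States study in which "the probability of downsizing for adults aged 55 years and older was higher among people with a higher loan-to-value ratio". It adds that economic fluctuations probably affect households differently, but that the Swedish pattern is not known.
- **Macroeconomic Trends and Health Factors** treats macroeconomic conditions descriptively and apart from the tax analysis.

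**The concern.** A difference-in-differences estimate can be read as a policy effect only if the two groups would have moved in parallel without the policy. With a single year on each side, the data used cannot speak to that assumption. Whatever changed differently for owners of high- and low-assessed homes between 2006 and 2010 enters the estimate together with the reform.

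The article supplies a candidate itself. A financial crash falls in the reform year, and Housing Policy Context describes owners in this age group as particularly exposed to house prices and interest rates. Exposure to the reform is defined by property value, so a house-price shock could plausibly act on the two groups unequally.

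At stake is the research question on how the 2008 reform affected the probability of moving. The Discussion argues that the national property tax allows a valid empirical test, and it expects economic policies to play an important role in decisions to stay. The two-year contrast alone cannot carry a causal policy statement of that kind.

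**Working it through.** The article states no alpha, power, effect size or move rate for this analysis, so there is no planned figure to reproduce. The dates agree: 2008 - 2 = 2006 and 2008 + 2 = 2010.

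**Step 1. Can trends be examined?** Write each group-by-year mean as an intercept, a group effect, year effects and a group-by-post term. Then add a group-specific linear trend and compare the number of parameters with the rank of the design matrix.

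| Years used | Cells | Parameters without trend (rank) | Parameters with trend (rank) |
|---|---|---|---|
| 2006, 2010 (as planned) | 4 | 4 (4) | 5 (4) |
| 2002, 2004, 2006, 2010 | 8 | 6 (6) | 7 (7) |
| 2000 to 2006 yearly, 2010 | 16 | 10 (10) | 11 (11) |

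The planned contrast is saturated: 4 - 4 = 0 degrees of freedom. With a differential trend it has five unknowns and rank four. Adding pre-reform years makes the trend estimable.

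**Step 2. What does the two-year contrast estimate?** Let r be the reform effect in the high relative to the low exposure group, cH and cL the downturn effects in the two groups, and d the differential trend per year. Over 2010 - 2006 = 4 years:

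DiD = r + (cH - cL) + 4d

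**Step 3. Illustration.** All values are assumed, in moves per 100 households, with r = 0.

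| cL | cH | d | DiD |
|---|---|---|---|
| -1.0 | -1.0 | 0 | 0.0 |
| -0.5 | -1.0 | 0 | -0.5 |
| -1.0 | -0.5 | 0 | +0.5 |
| -0.5 | -1.5 | 0 | -1.0 |
| -1.0 | -1.0 | 0.1 | +0.4 |

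The first row shows that a common downturn effect cancels. The others show that only the differential part biases the estimate, in either direction.

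**Step 4. Effect on a nominal 5% test.** This is again illustrative. Assume a 3% move rate, n households per cell, no reform effect, standard errors based on household sampling alone, and independent group-by-year shocks with standard deviation s.

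- Sampling SE = sqrt(4 × 0.03 × 0.97 / n), which is 0.153 points for n = 50,000.
- Shock SD of the DiD = 2s.
- False-positive rate = 2Φ(-1.96 × SE / sqrt(SE² + (2s)²)).

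For s = 0.1, 0.2 and 0.3 points the rate is about 24%, 49% and 63% with n = 50,000, and 9%, 20% and 33% with n = 10,000. No input comes from the article, which also states no variance method. These figures show a mechanism; they do not forecast this study's error rate.

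**The case against.** The strongest reply is that the article does not rely on the raw contrast. It lists three ways of adjusting for differences between the groups, its covariate list is introduced as examples, and an analysis plan that is not shown may add trend checks. This stands in part. A regression discontinuity in assessed value would not need parallel trends across the whole of both groups and might avoid the problem. But the running variable is not stated, and a cut-off in calendar time would share the confounding. Covariate control and matching balance observed characteristics; they neither test trends nor by themselves remove a shock tied to property value. An unseen plan could add checks, but the two-year contrast is stated outright.

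Three stronger readings are tempting, and the documents do not support them:

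- **That crash effects in general are attributed to the reform.** A common effect cancels; only a difference between the exposure groups remains.
- **That the article's own evidence shows the groups reacted differently.** The cited study is from the United States and concerns loan-to-value ratio, which the article does not tie to assessed value. The article calls the Swedish pattern unknown. Plausible is as far as this goes.
- **That the analysis uses covariates only as main effects, excludes mortgage debt, or understates its standard errors.** No model form or variance method is given, and the covariate list is open-ended.

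**Conclusion.** The point holds in a limited form. As fixed, the 2006-versus-2010 contrast cannot examine parallel trends. That follows from the design alone and needs no assumption. The estimate equals the reform effect plus any downturn effect or trend that differs between high- and low-assessed properties. The article makes such a difference plausible, but its size and direction in Sweden are unknown. The biases of -1.0 to +0.5 moves per 100 households and the false-positive rates of 9% to 63% rest wholly on assumed inputs and do not measure the actual problem.

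The matter concerns one of several research questions. A properly specified discontinuity in assessed value could ease it, but the text does not say that this is what is meant.

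**What to change.** Replace the two-year contrast as the main analysis with a multi-year event-study difference-in-differences, over the years for which the linked registers hold both moves and assessed value.

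- Fix exposure at pre-reform assessed value.
- Show yearly leads and lags, and run placebo reform dates before 2008.
- Leads and placebos test earlier trends but cannot separate a shock that begins in 2008. So also interact baseline region, income and, where held, mortgage debt or loan-to-value ratio with year, and show whether the effect persists in later post-reform years.
- State the remaining confounding with the crash as a limit on the conclusion.
- State the running variable and cut-off of the regression discontinuity.
- Keep 2006 versus 2010 as a descriptive summary.

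The cost is mainly analysis time. The longitudinal database spans 1968 to 2016, but no years are given for the property register or the income and taxation register, so their coverage must be confirmed before the window is set. New data collection is probably not needed. The price is more work and probably wider, less favourable intervals.
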